# Can telerehabilitation services combined with caregiver-mediated exercises improve early supported discharge services poststroke? A study protocol for a multicentre, observer-blinded, randomized controlled trial

**DOI:** 10.1186/s12883-021-02533-w

**Published:** 2022-01-17

**Keywords:** Stroke, Telerehabilitation, Caregivers, Exercise, Walking, Clinical trial protocol

## Abstract

**Background:**

Recovery of walking ability is an important goal for patients poststroke, and a basic level of mobility is critical for an early discharge home. Caregiver-mediated exercises could be a resource-efficient strategy to augment exercise therapy and improve mobility in the first months poststroke. A combination of telerehabilitation and face-to-face support, blended care, may empower patient-caregiver dyads and smoothen the transition from professional support to self-management. The Armed4Stroke study aims to investigate the effects of a caregiver-mediated exercise program using a blended care approach in addition to usual care, on recovery of mobility in the first 6 months poststroke.

**Methods:**

A multicentre, observer-blinded randomized clinical trial in which 74 patient-caregiver dyads will be enrolled in the first 3 months poststroke. Dyads are randomly allocated to a caregiver-mediated exercises intervention or to a control group. The primary endpoint is the self-reported mobility domain of the Stroke Impact Scale. Secondary endpoints include care transition preparedness and psychological functioning of dyads, length of inpatient stay, gait-related measures and extended ADL of patients, and caregiver burden. Outcomes are assessed at enrolment, end of treatment and 6 months follow-up.

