### Participants

Seventy-two patients with stroke, and 1 or 2 of their informal caregivers will be enrolled during in- or outpatient rehabilitation. The caregiver can be a partner, family member, or other person close to the patient. They are not healthcare professionals, nor are they paid for their efforts. Stroke is defined by the World Health Organization as “a clinical syndrome typified by rapidly developing signs of focal or global disturbance of cerebral functions, lasting more than 24 hours or leading to death, with no apparent causes other than of vascular origin” [22]. Subarachnoid haemorrhage, and stroke resulting from a brain tumour or traumatic brain injury are excluded as these subtypes differ in their prognosis.

Inclusion criteria for both patient and caregiver are: 1) 18 years or older; 2) written informed consent; 3) able to understand the Dutch language on sufficient level to understand instructions and complete the questionnaires; and 4) motivated for CME. Inclusion criteria for the patient are: 1) < 3 months poststroke; 2) living independently prior to stroke; 3) discharged or planned to be discharged home; 4) able to follow instructions (Montreal Cognitive Assessment [MoCA] score > 21 points); and 5) able and willing to appoint an informal caregiver. An additional inclusion criterion for the caregiver is: being medically stable and able to support the patient. A trained physiotherapist will judge safety and determine if caregivers are physically and mentally able to support the patient during an intake exercise session. Exclusion criteria for both patient and caregiver will be a serious comorbidity that interferes with participation, e.g., premorbid restrictions in mobility as a result of a neurological disease, congestive heart failure or fractures of the lower extremity. Patients will not be enrolled in other clinical trials during the study period.

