### Power analysis

We expect a significant improvement of 10 points (10%) on the SIS mobility domain (mean 79.4, SD 14) in favour of the intervention group. We expect that minimally 30 patients are required per trial arm [76]. Including 20% drop-outs (for patients and caregivers), a sample size of 72 patient-caregiver dyads is needed to achieve sufficient statistical power of 80% using a two-tailed significance level alpha of *p* < 0.05. Currently, 26 participants have been enrolled in the ongoing trial.

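### The abstract plans 74 dyads and the body plans 72; only 72 has a stated derivation, and after 20% drop-out it gives about 76% unadjusted power, not the stated 80%

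*Protocol article*

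**What the plan says.** The protocol article gives the planned enrolment in three places.

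- Abstract, Methods: a trial "in which 74 patient-caregiver dyads will be enrolled in the first 3 months poststroke".
- Methods, Participants: "Seventy-two patients with stroke, and 1 or 2 of their informal caregivers will be enrolled during in- or outpatient rehabilitation".
- Methods, Power analysis: "a sample size of 72 patient-caregiver dyads is needed".

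The Power analysis section also supplies the inputs. The assumed effect is given as "We expect a significant improvement of 10 points (10%) on the SIS mobility domain (mean 79.4, SD 14"). The evaluable number is given as "We expect that minimally 30 patients are required per trial arm". Loss is allowed for by "Including 20% drop-outs (for patients and caregivers"), and the result is tied to "sufficient statistical power of 80"% at a two-tailed alpha of 0.05. Allocation is 1:1 (Design section). The Data analyses section plans a linear mixed model that includes the baseline value of the outcome. When the article was written, 26 participants had been enrolled and recruitment was continuing.

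**The concern.** The three statements count the same thing. Each dyad has one patient, so the allowance of one or two caregivers per patient cannot turn 72 into 74. None of the three comes from an amendment history. A reader therefore cannot tell from the article alone why the abstract differs, and the trial was still recruiting towards the figure.

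The planned number should be stated one way, because it defines full enrolment when results are reported and because the power claim is attached to it. That second role prompts a further check: whether the 72 in the body delivers the stated 80% power after the stated 20% loss.

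**Working it through.** **Inputs.** Difference 10 points, SD 14, 30 evaluable per arm, 20% drop-out, 80% power, two-sided alpha 0.05 (all from Power analysis); 1:1 allocation (Design).

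**1. Reproducing the plan's figure.** 2 x 30 = 60 evaluable. 60 x 1.20 = 72, an exact match with Participants and Power analysis.

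**2. Looking for 74.** From the stated 30 per arm, 60 x 1.20 = 72 and 60 / 0.80 = 75; neither gives 74. Starting from 31 per arm, 62 x 1.20 = 74.4, which is close, but the article does not state 31 per arm or that route.

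**3. Evaluable number needed for 80% power.** By the normal approximation, n per arm = 2 x (1.960 + 0.842)² x 14² / 10² = 30.8, so 31. By the two-sample t-test, n = 31.8, so 32. The stated 30 per arm is close to both but slightly short: its power is 77.6% by the t-test (79.0% by the normal approximation).

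**4. Drop-out.** If a fraction d is lost from N enrolled, N x (1 - d) remain. Keeping 60 therefore needs N = 60 / (1 - 0.20) = 75. Multiplying by 1.20 falls short, because the 20% loss applies to the enlarged number: 72 x 0.80 = 57.6.

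**5. Power after 20% loss** (standardised difference 10 / 14 = 0.714, unadjusted, two-sided 0.05):

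| Enrolled | Evaluable | Per arm | t-test | Normal |
|---|---|---|---|---|
| 72 | 57.6 | 28.8 | 75.9% | 77.4% |
| 74 | 59.2 | 29.6 | 77.1% | 78.5% |
| 75 | 60.0 | 30.0 | 77.6% | 79.0% |

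The difference between 72 and 74 is 77.1 - 75.9 = 1.2 points. For 32 evaluable per arm after 20% loss, 64 / 0.80 = 80 dyads would be enrolled.

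**6. Effect of baseline adjustment.** The article gives no baseline-outcome correlation r, so the values here are assumptions. If 14 is the unadjusted SD of the outcome, the residual SD is 14 x sqrt(1 - r²). At 57.6 evaluable the t-test power is:

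| Assumed r | Residual SD | Power |
|---|---|---|
| 0.3 | 13.36 | 79.7% |
| 0.4 | 12.83 | 82.8% |
| 0.5 | 12.12 | 86.8% |

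**The case against.** The best defence is that the target can be identified. The two operative sections agree on 72 and the stated inputs produce it, so the abstract's 74 is an outlier. That stands. A reader might infer that neither figure follows from the plan, or that the article offers two equal enrolment targets and leaves the stopping point open. The document does not support either reading, since 72 is exactly 60 x 1.20 and is stated twice in the body.

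A reader might also infer that unblinded treating teams could choose between 72 and 74 with the results in view. The article does say that dyads and physiotherapists cannot be blinded and that the primary outcome is self-reported. But it describes no interim look and no access by treating teams to accumulating outcome data. It also places randomization with a researcher outside inclusion, assessment and delivery. It shows no mechanism by which two extra dyads would bias the comparison. Nor can anything be said about the trial register's figure, because that record is not at hand.

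On power, the defence is that the shortfall has nothing to do with the 72/74 mismatch and that the unadjusted t-test is not the planned analysis. Both are fair. The shortfall would exist if every section said 72, and it should not be used to make the mismatch look larger. Baseline adjustment could recover 80%, at an assumed correlation a little above 0.3. What remains is that the Power analysis section makes its claim without stating a correlation, without saying whether the SD of 14 is already adjusted, and without claiming any gain from the model.

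**Conclusion.** The contradiction is real but minor: 74 in the abstract against 72 twice in the body, with 74 probably a slip. It is worth two dyads and about 1 point of power, and it does not threaten the validity of the trial.

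The power statement is a separate point, and it also holds. On the stated inputs, 72 enrolled with 20% loss gives about 76% power, not 80%. The causes are a starting number of 30 per arm where the t-test needs 32, and inflation by 1.2 where division by 0.8 is needed. This rests on an unadjusted two-sided t-test and on patients who drop out contributing nothing to the analysis. Under the planned baseline-adjusted mixed model, 80% may well be reached, but the article does not give the assumption needed to show it.

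**What to change.** State one target number in the abstract, Participants and Power analysis, and show its derivation from the evaluable number per arm and the drop-out rate. Then do one of the following:

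- Restate the power this number delivers after 20% drop-out: about 76% at 72 or about 77% at 74, unadjusted.
- If 80% is claimed for the baseline-adjusted mixed model, state the baseline-outcome correlation assumed and say whether the SD of 14 is before or after adjustment.

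Either is a correction of the text. It needs no change to the design.

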**Results:**

During 8 weeks, caregivers are trained to become an exercise coach using a blended care approach. Dyads will receive a tailor-made, progressive training program containing task-specific exercises focusing on gait, balance, physical activity and outdoor activities. Dyads are asked to perform the training program a minimum of 5 times a week for 30 min per session, supported by a web-based telerehabilitation system with instruction videos and a messaging environment to communicate with their physiotherapist.

**Conclusions:**

We hypothesize that the Armed4Stroke program will increase self-reported mobility and independence in ADL, facilitating an early discharge poststroke. In addition, we hypothesize that active involvement of caregivers and providing support using blended care, will improve the care transition when professional support tapers off. Therefore, the Armed4Stroke program may complement early supported discharge services.

**Trial registration:**

Netherlands Trial Register, NL7422. Registered 11 December 2018.

**Supplementary Information:**

The online version contains supplementary material available at 10.1186/s12883-021-02533-w.

## Background

In 2017, approximately 104 million people were living with the consequences of stroke [1]. Most patients have long-term disabilities and remain dependent on informal caregivers [2]. Stroke rehabilitation is typically front-loaded, with resources mainly focused on inpatient care [3]. After discharge, professional support tapers off and the majority of home-dwelling stroke patients are physically inactive [4]. Caregivers provide sustained support and could promote self-generated physical activity [5]. However, caregivers often feel unprepared for their new caregiving role [6] and nearly half of community-dwelling stroke patients continue to report unmet needs across a range of clinical domains including mobility and emotional well-being [7]. Improving the transition from inpatient stroke rehabilitation to the community is identified as a high priority topic by the World Stroke Organization [8]. Early Supported Discharge (ESD) services were developed to improve the transition and facilitate community reintegration by accelerating inpatient discharge and providing an equivalent level of rehabilitation at home [9]. Although the content of an effective service is not clearly defined, it has been shown that ESD can reduce disability and long-term dependency [10]. However, a basic level of mobility such as the ability to stand up from a chair is critical for the possibility of an early discharge [11]. In addition, patients still experience an abrupt and disjointed care transition when professional support from an ESD team dwindles and caregivers would benefit from more support and training [12]. Hence, strategies to improve mobility in the first months poststroke and smoothen the care transition are needed to facilitate and complement current ESD services.

Training caregivers to become an exercise coach and perform Caregiver-Mediated Exercises (CME) may be a resource-efficient strategy to augment exercise therapy in the first 6 months poststroke [13]. Meta-analyses have shown that augmented exercise therapy and repetitive, progressive and task-oriented training can improve mobility and independence in Activities of Daily Living (ADL) in the first 6 months poststroke [14, 15]. In addition, involving caregivers in goal-setting and rehabilitation may smoothen the care transition by improving preparedness for discharge and enhancing self-efficacy in the home setting. A blended care approach, consisting of a combination of telerehabilitation and face-to-face support, is another promising paradigm to facilitate the transition from professional support to self-management [16]. Two recently conducted Randomized Controlled Trials (RCTs) showed that CME supported by an offline application with exercise videos was feasible, safe, and effective in improving psychological outcomes [17, 18]. In addition, dyads randomized to the CME intervention experienced a smooth transition to the home setting [19]. Unfortunately, the intervention did not improve self-reported mobility, nor were significant differences found for secondary outcomes of physical functioning. The neutral outcome may be explained by insufficient treatment contrast between the intervention and control group in terms of total exercise time, as a result of contamination. Interestingly, the Australian trial did find a reduction in Length Of Stay (LOS) in rehabilitation wards and a significant improvement of mobility and extended ADL in a per-protocol analysis of 20 patients that returned home during the intervention [17]. In addition to the CME program, this subgroup received telerehabilitation and home visits after discharge. Blended care and extending CME to the community, where caregivers can motivate the patient and provide continuity of exercises when professional support tapers off, could therefore be a promising addition to ESD services.

The Allied Rehabilitation using caregiver MEDiated exercises for Stroke (Armed4Stroke) study investigates a CME program using a blended care approach, in addition to usual care. Compared to previous trials, there is an increased focus on joint goal-setting and rehabilitation in the home situation to increase motivation and stimulate self-management. The training program is developed to achieve important milestones for community ambulation [20, 21] and dyads are supported by a web-based telerehabilitation system with individualized goals, exercise videos and a messaging environment to communicate with their physiotherapist.

The aim of this paper is to describe the Armed4Stroke study design following the SPIRIT Statement (Additional file 1: SPIRIT Checklist). The multicentre, observer-blinded trial aims to assess the effects of the Armed4Stroke program in addition to usual care, starting during the subacute phase poststroke. We hypothesize that the Armed4Stroke program will:Increase patients’ self-reported mobility;Smoothen the care transition, resulting in reduced LOS and better preparedness for discharge;Improve psychological functioning of patients and caregivers, such as mood and self-efficacy.

## Methods

### Design

The Armed4Stroke study is designed as a multicentre, observer-blinded, phase II, randomized controlled superiority trial with two parallel groups. Patient-caregiver dyads will be randomly allocated at a 1:1 ratio to 8 weeks of CME and telerehabilitation (Armed4Stroke program) in addition to usual care, or usual care alone. The trial is registered since 11 December 2018 in the Netherlands Trial Register as NL7422. The study protocol was approved by the Medical Ethics Review Committee of VU Medical Centre on April 30th 2019 and is registered with trial number 2019.081 - NL67357.029.18.

### Setting

The multicentre study is conducted in the in- and outpatient clinics of 4 rehabilitation centres in the Netherlands: 1) Reade Rehabilitation, Amsterdam; 2) Roessingh, Centre for Rehabilitation, Enschede; 3) Sint Maartenskliniek, Nijmegen; and 4) Vogellanden, Zwolle. The Amsterdam UMC, location VU Medical Centre, is the initiator of this study in collaboration with Amsterdam Rehabilitation Research Centre | Reade and Roessingh Research and Development, Enschede.

### Participants

Seventy-two patients with stroke, and 1 or 2 of their informal caregivers will be enrolled during in- or outpatient rehabilitation. The caregiver can be a partner, family member, or other person close to the patient. They are not healthcare professionals, nor are they paid for their efforts. Stroke is defined by the World Health Organization as “a clinical syndrome typified by rapidly developing signs of focal or global disturbance of cerebral functions, lasting more than 24 hours or leading to death, with no apparent causes other than of vascular origin” [22]. Subarachnoid haemorrhage, and stroke resulting from a brain tumour or traumatic brain injury are excluded as these subtypes differ in their prognosis.

Inclusion criteria for both patient and caregiver are: 1) 18 years or older; 2) written informed consent; 3) able to understand the Dutch language on sufficient level to understand instructions and complete the questionnaires; and 4) motivated for CME. Inclusion criteria for the patient are: 1) < 3 months poststroke; 2) living independently prior to stroke; 3) discharged or planned to be discharged home; 4) able to follow instructions (Montreal Cognitive Assessment [MoCA] score > 21 points); and 5) able and willing to appoint an informal caregiver. An additional inclusion criterion for the caregiver is: being medically stable and able to support the patient. A trained physiotherapist will judge safety and determine if caregivers are physically and mentally able to support the patient during an intake exercise session. Exclusion criteria for both patient and caregiver will be a serious comorbidity that interferes with participation, e.g., premorbid restrictions in mobility as a result of a neurological disease, congestive heart failure or fractures of the lower extremity. Patients will not be enrolled in other clinical trials during the study period.

#### Baseline characteristics

Demographic and social characteristics of patients and caregivers will be recorded at baseline including: age, sex, country of birth, level of education, type and duration of relationship, living arrangement, work status, and comorbidities following the Cumulative Illness Rating Scale [23]. In addition, we will document stroke characteristics: type and location, stroke severity following the Bamford classification system [24], date of stroke, previous stroke, hemiplegic side, presence of sensory deficits, hemianopia, neglect or aphasia, communicative ability following item 19 of the Utrecht Communication Observation [25], and cognition following the MoCA [26].

### Study procedures

Every patient with stroke, starting in- or outpatient rehabilitation is screened for eligibility according to the inclusion and exclusion criteria by their rehabilitation physician and/or physiotherapist. Eligible dyads receive verbal and written information about the study. If a dyad wants to participate after a reflection period of 1 week, the intake exercise session is scheduled. Upon enrolment, informed consent will be signed by patient and caregiver(s) (Additional file 2: Informed consent form) and primary and secondary endpoints are measured by an independent assessor (MM, CN). Following the assessments, an activity monitor is worn by the patient for 1 week and dyads are randomized to the intervention or control group at a 1:1 ratio using an online randomization module with a minimization algorithm to prevent unequal group sizes. The module will be managed by a researcher (EW, GK) from the initiating institute, not involved in inclusion, assessment or intervention delivery. Factors in the minimization include: 1) centre; 2) inpatient versus outpatient; 3) ≥70 years versus < 70; and 4) Functional Ambulation Category (FAC) 5 versus FAC < 5. Primary and secondary endpoints are repeated by a blinded assessor (MM) at the end of treatment and 6 months follow-up (Fig. 1: Study design). During the study period, serious adverse events will be recorded and reported to the Medical Ethics Review Committee of VU Medical Centre. Data collection is done using electronic Case Report Forms (eCRFs) within the Good Clinical Practice-proof, cloud-based clinical data management platform Castor EDC [27]. The study is monitored by the independent clinical research bureau from VU medical centre. Univariate checks, e.g., range checks, and conditional variables are built-in the eCRFs. The first participant was enrolled on September 2nd 2019 and participants are currently being recruited and enrolled.

**Fig. 1 Fig1:**
[figure not shown]
Study design

### Armed4Stroke intervention program

The Armed4Stroke program consists of 8 weeks of complementary exercises executed with a caregiver (CME), in addition to usual care. A trained physiotherapist compiles a tailor-made, progressive training program, containing personal goals and task-specific exercises focusing on balance, gait, outdoor activities and physical training. A total of 31 goals and 80 exercises according to evidence-based physical therapy guidelines [28] were developed to achieve important milestones for community ambulation, based on expert’s opinion and items of the hierarchical Mini-BESTest [29] and Rivermead Mobility Index (RMI) [30]. Dyads are asked to perform the exercises minimally 5 times a week for 30 min per session. This intensity is in line with current exercise guidelines [28] and was shown to be feasible in previous CME studies [17, 18]. Dyads are advised to execute their program outside usual training hours and during weekends, when patients are mostly inactive [31, 32].

Dyads are supported by a trained physiotherapist during at least 4 face-to-face sessions, scheduled every other week. During the first session, the program is explained in detail and explicit attention is given to information about the influence of physical activity and exercise on mood and health-related quality of life [33]. In addition, the role of caregivers and their benefits will be discussed. During subsequent sessions, the program is adapted according to the progress and personal goals of dyads, barriers are identified and addressed, and dyads are motivated to continue their exercise program. During the program, dyads are supported by exercise videos which are built into a web-based telerehabilitation system. Telerehabilitation poststroke should not be restricted to a time, place or device [16]. Therefore, the web-based system can be accessed on all devices with an internet connection including a computer, tablet or smartphone. In addition, dyads can communicate a-synchronically (i.e., exchange messages independent of time) with their physiotherapist. Therapists can use the telerehabilitation system to set-up goals and exercises, monitor compliance and progress, give feedback and motivate participants. Physiotherapists were extensively trained in applying the program to optimize standardization.

